### **11.3.3 Interim analyses**

A planned interim analysis will be carried at mid point of the trial (after half the patient had been entered and completed). The interim analysis will solely concern itself with the primary end point and will compare the proportion of newly detected AF between the study groups.

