| Statistical Considerations: | Categorical variables will be reported as counts and percentages; continuous variables will be reported as mean and SD or as median with 25% to 75% interquartile range according to their distribution. Normality will be assessed by visual inspection of histograms, the computation of Q-Q plots and the shapiro-wilk test. Categorical variables will be compared using chi-square or Fisher's exact test as appropriate. Continuous variables will be analyzed using the Student's t-test or the Wilcoxon rank-sum test according to their distribution. Survival free from the occurrence of clinical end points will be compared using the log-rank test and plotted as Kaplan-Meier survival functions. All statistical analyses will be performed using dedicated software (Stata version 13, StataCorp LP, College Station, Texas) at a 2-tailed significance level of $\alpha = 0.05$ . |
| GCP Statement:              | This study will be conducted in compliance with the protocol, the current version of the Declaration of Helsinki, the ICH-GCP or ISO EN 14155 (as far as applicable) as well as all national legal and regulatory requirements.                                                                                                                                                                                                                                                                                                                                                                                                                                                                                                                                                                                                                                                                     |

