## **2.8 Early termination of the study**

The Sponsor-Investigator (and any competent authority) may terminate the study prematurely according to certain unforeseen circumstances. These may include but are not limited to:

- ethical concerns,
- insufficient participant recruitment,
- when the safety of the participants is doubtful or at risk, respectively,
- alterations in accepted clinical practice that make the continuation of a clinical trial unwise,
- early evidence of benefit or harm of the experimental intervention

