## **11. STATISTICAL METHODS**

Categorical variables will be reported as counts and percentages; continuous variables will be reported as mean and SD or as median with 25% to 75% interquartile range according to their distribution. Normality will be assessed by visual inspection of histograms, the computation of Q-Q plots and the shapiro-wilk test. Categorical variables will be compared using chi-square or Fisher's exact test as appropriate. Continuous variables will be analyzed using the Student's t-test or the Wilcoxon rank-sum test according to their distribution. Survival free from the occurrence of clinical end points will be compared using the log-rank test and plotted as Kaplan-Meier survival functions. All statistical analyses will be performed using dedicated software (Stata version 13, StataCorp LP, College Station, Texas) at a 2-tailed significance level of  $\alpha = 0.05$ .

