### **11.2 Determination of Sample Size**

Based on previous research, the expected annual detection rate is 3% in the Zenicor group and 1% in the control group. The inclusion of  $n=745$  patients per group would yield a power of 80% and a significance of  $\alpha = 0.05$  to detect that difference. In order to account for ineffective measurements, post-inclusion drop-outs or other unforeseen drop-outs, we seek to include  $n=800$  patients per group.

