### **11.3 Planned Analyses**

#### **11.3.1 Primary Analysis**

The primary analysis pertains to the proportion of newly detected atrial fibrillation. The primary analysis will compare the proportion of newly detected AF between the intervention and the control group. Univariate methods (Chi-Test) will be employed. If a significant difference in baseline characteristics will be observed, then logistic regression will be performed in order to correct for baseline imbalances.

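### The half-way interim compares the arms on the primary endpoint with no stated boundary or adjusted final level; if an interim p<0.05 is acted on or claimed, overall type I error would be about 8.3% rather than 5%

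*Protocol*

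**What the plan says.** - **Interim (Protocol 11.3.3).** There is one planned look, "after half the patient had been entered and completed". It is confined to the primary endpoint and "will compare the proportion of newly detected AF between the study groups". No purpose, boundary, alpha split, adjusted final level or consequence is given.
- **Primary analysis (Protocol 11.3.1).** "The primary analysis will compare the proportion of newly detected AF between the intervention and the control group", by chi-square test. The interim therefore makes the same comparison on part of the data.
- **Significance level (Protocol 11 and synopsis).** The sentence beginning "All statistical analyses will be performed using dedicated software" ends by fixing the level, given in the synopsis as a "2-tailed significance level of $\alpha = 0.05". No analysis is exempted.
- **Sample size (Protocol 11.2).** For 3% against 1%, 745 per group "would yield a power of 80% and a significance of" 0.05; 800 per group are to be included to cover drop-outs and ineffective measurements. The interim is not mentioned.
- **Early termination (Protocol 2.8).** A non-exhaustive list of grounds includes "early evidence of benefit or harm of the experimental intervention", with no numerical criterion.

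**The concern.** Read together, these sections permit the primary null hypothesis to be tested twice, each time at the full 0.05, with termination for benefit available and no rule to govern it. Two unadjusted tests give more than a 5% chance of a false positive.

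The situation is likely to arise. If the protocol's own assumptions are right, the interim is slightly more likely than not to give p<0.05 (shown below). The team would then hold a nominally significant result in an open-label trial, with early benefit listed as a ground for stopping and nothing to say whether that result is enough. Stopping on it would tend to overstate the detection gain, and could leave fewer patients for the outcomes at 2, 5 and 10 years. A boundary chosen after the interim has been seen would carry little credibility.

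**Working it through.** **Inputs.** Two-sided alpha 0.05 (Section 11, synopsis); information fraction 0.5 (11.3.3); chi-square test (11.3.1); 1% against 3%, 745 per group needed and 800 planned (11.2); allocation 1:1 (6.1).

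**1. The protocol's own sample size.**
- The unpooled formula, n = (1.960 + 0.842)² × (0.01×0.99 + 0.03×0.97) / 0.02², gives 766 per group; the pooled version gives 769.
- At 745 per group, power is 78.8% by the normal approximation and 81.2% by exact enumeration of the uncorrected chi-square test.
- The stated 745 is therefore reasonable for 80% power. It is a single-look figure at the full 0.05.

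**2. Type I error with two looks at 0.05.** Under the null, the interim and final statistics are approximately bivariate normal with correlation √0.5 = 0.707.
- Overall error = 1 − P(|Z₁|<1.96 and |Z₂|<1.96) = 1 − 0.9169 = **0.0831**.
- If only significant benefit stops the trial at the interim and the final test is two-sided: 1 − P(Z₁<1.96 and |Z₂|<1.96) = **0.0666**.
- If the interim can trigger neither a stop nor a claim: **0.05**.
- If the look falls at 40% or 60% of the information instead: 0.0863 or 0.0796.

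**3. The same check with the chi-square test itself** (simulated null trials, 400 then 800 per group, rejection at either look):

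| Common detection rate | Interim alone | Final alone | Either look |
|---|---|---|---|
| 1% | 4.4% | 4.7% | 7.7% |
| 2% | 4.6% | 5.1% | 8.1% |
| 3% | 5.0% | 5.1% | 8.4% |

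The final test alone is close to 5%; the excess comes from the interim.

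**4. What the interim would show under 1% against 3%.**
- Expected counts are 4/400 and 12/400. z = 0.02 / √(0.02×0.98×2/400) = 2.02, p = 0.043 (uncorrected chi-square).
- The exact probability of p<0.05 at 400 per group is 52.7%.
- Among trials that cross, the mean observed difference is 2.7 points against a true 2.0.

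**5. Boundaries that hold 5%, and their cost.** Crossing probability (400 per group) and final power (800 per group) are exact chi-square figures under 1% against 3%.

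| Interim p / final p | Overall error | Chance of crossing at interim | Power of final test |
|---|---|---|---|
| 0.05 / 0.05 (no boundary) | 8.3% | 52.7% | 83.9% |
| 0.001 / 0.0498 (Haybittle-Peto type) | 5.0% | 7.4% | 83.9% |
| 0.0052 / 0.0480 (O'Brien-Fleming) | 5.0% | 19.6% | 82.9% |

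The power column assumes that all 800 per group can be analysed. By the normal approximation, the O'Brien-Fleming final level gives 81.1% against 81.6% at 0.05.

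**The case against.** **No decision rule is stated.** A reader might infer that the trial's type I error simply is 8%. The protocol does not support that: nowhere does it say that an interim p<0.05 stops the trial or supports a claim. If the look triggers nothing, the error is 5%. This stands, and the size must be given conditionally.

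**Section 2.8 is generic.** A reader might also take its benefit bullet as the interim's efficacy rule. The list concerns unforeseen circumstances, does not mention the interim, and is not cited in 11.3.3. This also stands: the link is permitted by the text but not made by it. However, 11.3.3 is the only planned between-group look before the end, and nothing declares it non-binding or restricts it to futility or safety.

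**A separate SAP may hold a boundary.** It may, and the most that can be said is that the protocol states none. But the protocol is not merely silent. It fixes 0.05 for every analysis, so an SAP boundary would conflict with Section 11 and the synopsis.

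**Some consequences depend on further choices.** The p of 0.043 is for the uncorrected chi-square; the Yates correction gives 0.077 and Fisher's exact test, which Section 11 allows where appropriate, 0.074. A stop would halve the long-term cohort only if enrolment paused while the first half completed, and no pause is stated. Both points limit the illustration, not the error calculation.

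**Conclusion.** The point holds in conditional form. As written, the protocol permits two tests of the primary hypothesis at the full 0.05 and does not say what the first may trigger. The overall type I error therefore depends on an unstated rule:

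- 5% if the interim can lead to no stop and no claim;
- about 6.7% if only significant benefit stops the trial;
- about 8.3% if significance in either direction is acted on or claimed.

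These figures assume one look at half the information. The 745 per group is not in dispute, and leaving the look out of the sample size matters little, because a suitable boundary costs about one percentage point of power or less. The correction is needed before the interim because it concerns the error rate of the primary claim and, under the assumed rates, the chance of a nominally significant interim is 52.7%.

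**What to change.** Choose one route and write it into Section 11.3.3.

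1. **Efficacy stopping allowed.** State one boundary that holds 5% overall, as an explicit exception to the 0.05 in Section 11 and the synopsis. Examples are two-sided p<0.001 at the interim with 0.0498 at the final test, or O'Brien-Fleming at about 0.005 then 0.048. The two are not interchangeable, since the second stops more often at the interim, but both control the error. Tie the benefit part of the Section 2.8 bullet to the chosen boundary.
2. **No efficacy stopping.** State that the interim cannot lead to an efficacy stop or claim. Remove only benefit from the Section 2.8 bullet, keeping harm, and leave the final test at 0.05.

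If a separate SAP already contains a boundary, reconcile it with the protocol's 0.05 for all analyses.

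The cost is protocol wording. No extra patients are needed.

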### **11.3.4 Deviation(s) from the original statistical plan**

All deviations from the original statistical analysis plan will be provided in the final clinical study report.

## **11.4 Handling of missing data and drop-outs**

Missing data will be omitted pairwise from the analyses. Whenever data is missing, it will be explicitly stated in the final results of the study. Missing data arising from a loss to follow-up will be censored. The number of drop-outs will be provided in a flow-chart along with the reasons for said drop-out.

## **12. QUALITY ASSURANCE AND CONTROL**

The principal investigator will be responsible for proper training of all involved study personnel. All involved personal at University and Hospital Fribourg will be trained by the Zenicor Incorporation before starting to use the device. Additional training will be provided upon request.

### **12.1 Data handling and record keeping / archiving**

During the clinical trial, data will be accurately recorded and the original documents will be archived at the clinical trials unit at University and Hospital Fribourg. At the end of the study, Zenicor ECG will be saved in PDF form and stored for 10 years in the Zenicor-EKG Back-end system. All data collected will not include identifiable references to the subjects. The subject's anonymity will be maintained and the confidentiality of records and documents that could identify subjects will be protected.

#### **12.1.1 Case Report Forms**

Patient characteristics, procedural characteristics, study outcomes and clinical follow-up will be recorded on electronic Case Report Forms (REDCap). For each enrolled study participant one single CRF is drafted.

#### **12.1.2 Specification of source documents**

Source document will contain demographic data, cardiovascular risk factors, laboratory results and information about the follow up. CRF, Informed Consent Forms, Zenicor ECG and echocardiography will be found at the site of study.

### **12.1.3 Record keeping / archiving**

1 lead-ECG will be stored in the Zenicor system throughout the whole study. Individual reports for each patient will be downloaded as pdf, including all or selected ECG's and will be exported for local archiving.

## **12.2 Data management**

### **12.2.1 Data Management System**

Patients data will be transcribed with RED cap Software to create electronic CRF, designed to capture study information. A trained study nurse will complete data management procedures, including coding through a computer generating de-identified number (random.org), verification, validation, security and storage of the database.

### **12.2.2 Analysis**

Analysis of data will be performed using STATA MP 13 (Stata Inc., College Station, TX, USA).

### **12.2.3 Electronic and central data validation**

The Zenicor ECG will be transmitted to a central server for clinical analysis of the data. The investigators will interpret the validity and diagnosis on the displayed results.

## **12.3 Monitoring**

The following assessment for a minimal risk study are completed:

- Study poses no more risk than expected in daily life (no risk in the skin-contact to the thumbs of the patient to the zenicor electrodes, routine blood draw, physical exam).
- No vulnerable population included
- Trial procedures is not clinically unusual and complex

A possible misinterpretation of Zenicor electrocardiograms could lead to diagnostic errors and to unadapted treatment. The zenicor method has shown a sensitivity of 96% and specificity of 92% in detection and diagnosis of atrial fibrillation when compared with 12-lead ECG. The somewhat lower specificity reflects that the device rather overdiagnose than neglect patients with atrial fibrillation.

However, each case of newly diagnosed atrial fibrillation by use of the Zenicor device will be examined by two independent cardiologists. In case of uncertainty, additional recordings (by Holter or R-Test) will be made. The risk of diagnostic errors is very close to the usual risk taken in routine practice.

An external monitoring of the study will be carried out retrospectively and prospectively:

- 1st on-site visit, intermediate visits and closing visit

- study risk analysis
- verification of source data
- CRF verification
- revision of consent forms
- verification of the recruitment procedure
- validation of eligibility criteria
- evaluation of the main evaluation criterion
- evaluation of Serious Adverse Reaction Assessment (SAE)

## **12.4 Confidentiality, Data Protection**

Data will be stored physically and electronically on the personal computers at the clinical trials unit at University and Hospital Fribourg. Physical data are protected by the restricted access to their location with only the involved medical personnel having access to it. Electronical data are protected by the *IT-Services of Etat de Fribourg SITEL*. The investigators will have access to the protocol, dataset, and statistical code, during and after the study for publication and dissemination. The study nurse will only have access to the dataset during the study time.

### **12.3.1 Data protection and Storage at Zenicor (SWEDEN)**

All communication between the web browser and the Zenicor server is encrypted with 128 bits encryption with SSL (HTTPS). To login, user-ID and password is needed. All login attempts are logged with date and time. After 5 unsuccessful logins, the user-ID is blocked. The user can only view and access patients in the organization connected to the user. 2-factor authentication login can be provided upon request.

The communication from the server to internet is duplicated and protected by a firewall and a Web Application Firewall (WAF). The WAF filters, monitors and blocks HTTPS traffic to and from the web application. Administration of server is performed only by authorized personnel connecting via VPN.

All transactions in the database are logged in a transaction log. All changes in the ECG-database made by any user are logged by the server. If a user updates or deletes patient data and/or ECG recordings, the transactions are logged with date, time, user name and organizational unit. System logs are retained for 1 year.

The Zenicor server is located in an ISO27001 certified secure data center. The Data Center has physical access control, fire protection, climate control and equipment for uninterrupted power supply including use of independent electric generators.

The database of the master server is replicated to a slave server. A back-up of both master and slave is performed every 24h.

### **12.3.2 Security of data transmission between Fribourg and Sweden**

All communication between the device and the back-end system is performed over a GPRS-link and sent as a HTTP POST. When the patient has recorded an ECG and requests transmission of ECG, the

device will perform a start-up of the modem. The device then sets up a link to the GSM network. When link is up the device sends one or more measures. After each measurement is sent, the backend system (containing the ECG database) sends an acknowledgment that the ECG is successfully received to the device. When done sending all measurements, the modem is turned off.

If the device does not receive an acknowledgement from the backend system that transmission was successful, the device will re-send the ECG at the next requested transmission occasion. The device can store up to 200 unsent ECG's in case GPRS link cannot be established, data transmission fails to be acknowledged or if transmission is simply not requested by the patient.

The ECG is sent from the device as unprocessed raw data from the AD-converter. The raw measurement data has each measurement sample represented by 3 bytes, which is how the ADC encodes each measurement sample. All post-processing including signal processing and creation of an ECG image is performed by the backend system.

The ECG is sent without any patient identification information, but only device serial number. The device has no information of who is using the device, but only records, labels the ECG with the device serial number/time of recording and then transmits the ECG. The ECG is recognized by the backend system through the device serial number. As the backend system has the information of which patient is currently using the specific device ID, the ECG labeled with a corresponding device ID and time stamp can be connected to correct patient in the ECG database.

## 13. FUNDING AND SUPPORT

### 13.1 Budget

|                                      | Estimated cost in CHF |
|--------------------------------------|-----------------------|
| Personnel Costs               |                       |
| Study Nurse 50%                      | 60'000                |
| Devices and Equipements       |                       |
| Zenikor handheld ECG x12             | 12'000                |
| Barcode reader x12                   | 2'000                 |
| Publication and Dissemination |                       |
| Travel expenses for Dissemination    | 5'000                 |
| Congress fees                        | 2'000                 |
| Estimated total cost   | 81'000  |

### 13.2 Funding

The trial will be funded by the *Fonds Scientifique Cardiovasculaire Fribourg*. All external public or private institutions contributing to the trial will provide unrestricted grants to the *Fonds Scientifique Cardiovasculaire Fribourg* during the study periode. However, these parties still need to be defined.

## **15. APPENDICES**

1. Technical overview Zenicor ECG
2. Investigator's CV
3. Investigator's proof of GCP training
4. Case Report Forms
5. Patient informed consent (D/F)
